##### Algorithm Under Test

The PneumoWave Hub receives and transmits biosensor data to a cloud storage facility. The stored data are then processed in the cloud using experimental algorithms for the presence of reduced chest movement events in adults.

The performance of the algorithm under test will be compared to the reference events at the SIF in terms of the AUT’s sensitivity and false alarm rate. If the target numbers for sample size, injecting visits, and acute events are not reached, the analysis will still be possible and feasible.

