**Conclusions:**

This protocol establishes a foundation for advancing wearable technology in opioid overdose prevention within SIFs. The study will provide chest wall movement data and associated overdose data that will be used to train an algorithm that allows the biosensor to detect an overdose. The study will contribute crucial insights into OIRD, emphasizing the biosensor’s potential step forward in real-time intervention strategies.

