### Objectives

The objectives of the study are (1) to capture chest motion data using the PneumoWave biosensor, and staff-measured outcomes as the clinical reference (including clinical identification of an acute event), during instances of opioid injection and potential opioid overdose by attendees at a SIF, to develop and refine the overdose detection algorithm and (2) to examine acceptability to SIF attendees of the chest biosensor.

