### Study Design

This is an observational pilot study. Over 6 months, this study aims to capture approximately 40 overdose events that occur for consenting participants who are wearing the chest sensor during visits to inject at the SIF. Participants who consent to take part will be assigned an anonymous, numerical study ID number that will be linked to subsequent visits that they make to the SIF.

Chest motion data will be collected on the device securely and pseudo-anonymously (ie, pseudonyms will be used; no personally identifiable information will be stored alongside chest motion data) and streamed to a secure cloud. A SIF is designed to respond to a broad spectrum of adverse drug reactions, recognizing that not all incidents may escalate to an opioid overdose (thus any event that is attended to and requires prompting by staff is termed an “acute event”). The data collected here will be used to test and further develop chest wall movement “signatures” to accurately detect an “acute” drug event or potential overdose, as diagnosed by the current clinical observations in the SIFs. Wearing the device will not alter the services participants receive at the SIF and the sites will manage each acute event as per their standard protocols.

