### PneumoWave Managed Biosensor Data

As soon as the biosensor chest placement has been carried out, chest movement data will commence being captured. Data from the biosensor will be uploaded securely and automatically to a Data Hub stored in a small container, located within the SIF (Figure 2).

The data storage platform (supplied by Galen Data) complies with HIPAA (Health Insurance Portability and Accountability Act) requirements as set forth in the Galen Cloud HIPAA Compliance Matrix (004-0020), General Data Protection Regulation (GDPR) requirements as set forth in the Galen Cloud GDPR Compliance Matrix (004-0021), and California Consumer Privacy Act (CCPA) requirements. Additionally, Galen Cloud deployed on Amazon Web Services (AWS) is Health Information Trust Alliance (HITRUST) certified.

PneumoWave will review both chest movement data stored within the Galen Cloud and study data, including baseline questionnaire, injecting event, acute event, and satisfaction questionnaire data.

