## Discussion

There has been a recent surge of interest in mobile health and wearable devices to treat opioid use disorders [18,19] and specifically to detect and respond to opioid overdoses. However, there is limited research on detecting true overdose (which requires intervention) and the effectiveness of these devices to detect overdose in the community has not yet been adequately evaluated. A chest sensor that reliably detects the overdose breathing signature could alert the emergency services and save lives when fully developed and used in the community.

This observational study aims to capture chest motion data while participants wear a small chest-worn biosensor within medically supervised injecting centers in Australia. The data collected here will be used to test and develop respiratory “signatures” to accurately detect an acute or potential opioid overdose. Testing will allow for the differentiation of patterns that occur following opioid use but do not result in an overdose.

It is anticipated that this study will capture chest motion data from the sensor while participants inject opioids and it is likely that some instances of potential overdose will also be captured by the sensor. It is uncertain how much chest motion data will be corroborated with staff-measured outcomes. It is anticipated that the sensor will be considered positively overall among participants.

The findings of this study will be compared to a previous study of this chest sensor among participants who wear the sensor at home and are on opioid agonist treatment (paper in preparation), as well as other studies on wearable devices that have been examined acceptability and feasibility of varied technologies to combat the overdose crisis [20-25]. The potential effectiveness and acceptability of these studies are varied. Generally, there is limited but expanding research in this area with studies focused on products or technologies that are relatively new or in early development [12]. There is no published work on a remote chest sensor that can reliably detect chest wall movement in the context of an opioid overdose.

The strengths of this study are that it examines the effectiveness of the chest sensor among people who are injecting opioids in a relatively controlled but real drug-using environment. Research within an SIF is a unique opportunity to address external validity as participants will be those who the sensor is eventually intended for.

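### The same SIF recordings train and test the algorithm, so unless its version is fixed before scoring, the reported sensitivity will be optimistic

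*Protocol article*

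**What the plan says.** The protocol article gives the data of this one study two roles.

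- **Development.** The Objectives section states that chest motion and staff-measured outcomes are captured "to develop and refine the overdose detection algorithm". The Conclusions of the Abstract say that the data will be "used to train an algorithm that allows the biosensor to detect an overdose".
- **Testing.** Study Design names both uses in one sentence: "The data collected here will be used to test and further develop chest wall movement" signatures. The Discussion repeats this: "The data collected here will be used to test and develop respiratory" signatures.

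Algorithm Under Test then sets out the evaluation: "The performance of the algorithm under test will be compared to the reference events at the SIF", measured by sensitivity and false alarm rate. The only SIF reference events described are those of this study. The same section says "The stored data are then processed in the cloud using experimental algorithms", in the plural, and identifies no fixed version. It adds that the analysis can still be done if the targets for participants, visits and events are missed.

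Under PneumoWave Managed Biosensor Data, the device company has access to both signal and labels: "PneumoWave will review both chest movement data stored within the Galen Cloud and study data", and the study data listed there include acute events.

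**The concern.** If features, thresholds or the choice among candidate algorithms are tuned on a set of events, and sensitivity is then computed on those same events, the result describes fit to the development data. It does not describe what a new participant could expect. The gap is widest when events are few, which is the situation here.

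Sensitivity and false alarm rate are the only algorithm performance measures the article names. The Abstract's Methods say the sensor's ability to detect respiratory depression will be compared with staff-identified events, and the Discussion counts it as a strength that the study looks at the sensor's effectiveness in a real drug-using setting. An in-sample sensitivity cannot carry that reading.

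**Working it through.** **1. Event counts (Sample Size and Results).** The plan expects about 40 events in 4000 visits, hence 4000 − 40 = 3960 non-events. By April 2024 there were 10 overdoses in 1145 injecting events, hence 1145 − 10 = 1135 non-events and a rate of 10/1145 = 0.87%.

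The plan's own 40 does not follow from its inputs: 4000 × 1.2% = 48. The figure is worded as approximate and nothing below depends on it. A run with 48 events gave nearly the same optimism as 40 (0.805 v 0.754 with 1 feature, 0.822 v 0.691 with 20).

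**2. Assumptions, none of them in the documents.** Independent visits; p normally distributed features with unit variance; one feature shifted by 1.5 SD in events and the rest noise; a linear discriminant with pooled covariance; cut-off t at the Youden optimum; 200 repetitions.

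**3. Formulas.** With weights w and event mean μ:

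- apparent sensitivity = share of the development events scoring at least t
- true sensitivity = 1 − Φ((t − w′μ)/√(w′w))
- true false alarm rate = 1 − Φ(t/√(w′w))
- optimism = apparent − true

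**4. Results.**

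| Events / non-events | Features | Apparent sensitivity | True sensitivity | Optimism (points) | False alarm rate, apparent v true |
|---|---|---|---|---|---|
| 10 / 1135 | 1 | 0.854 | 0.725 | 12.9 | 0.213 v 0.215 |
| 10 / 1135 | 5 | 0.864 | 0.645 | 21.9 | 0.177 v 0.178 |
| 10 / 1135 | 10 | 0.881 | 0.595 | 28.6 | 0.170 v 0.174 |
| 10 / 1135 | 20 | 0.920 | 0.470 | 45.0 | 0.132 v 0.137 |
| 40 / 3960 | 1 | 0.813 | 0.762 | 5.1 | 0.230 v 0.230 |
| 40 / 3960 | 5 | 0.809 | 0.730 | 7.9 | 0.210 v 0.210 |
| 40 / 3960 | 10 | 0.821 | 0.717 | 10.4 | 0.208 v 0.209 |
| 40 / 3960 | 20 | 0.834 | 0.681 | 15.3 | 0.194 v 0.197 |

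The false alarm rate moves by at most 0.5 points. With no informative feature at all, the optimism in sensitivity is larger (for example 0.593 v 0.463 with 40 events and 1 feature), and the false alarm rate still moves by no more than 0.8 points.

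**5. A second mechanism: choosing among versions.** Assume 10 correlated candidates, each with true AUC 0.80, about 1,100 non-events and a 5% false alarm rate. Picking the best on 10 events gives an apparent sensitivity of about 0.49 to 0.54 against a true 0.33. On 40 events it gives about 0.42 to 0.44 against 0.34. Because all versions are equally good here, the whole gain is optimism by construction, so this supports the direction more than the size.

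**6. Clustering.** The 1145 injecting events come from 47 participants, about 1145/47 = 24 each. The simulation ignores this. Repeat visits by one person could enlarge the optimism, and a split by visit would put the same person on both sides.

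**The case against.** The strongest reply is that the article does not fix the order of work. Testing and further developing signatures could mean scoring an existing algorithm first and refining it afterwards, and a score taken before refinement carries none of this optimism. A condensed article may also leave data splitting, resampling and version locking to the full protocol or the analysis plan, neither of which is shown. Both points stand. The conclusion is therefore conditional, and it rests on the stated dual use of the data, not on the lack of a validation section. Nothing shown removes the condition.

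The study is also an observational pilot, and effectiveness is left to a later randomized investigation. That lowers the stakes but does not make an in-sample sensitivity interpretable.

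Four stronger readings are tempting, and the documents do not support them:

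- **That the false alarm rate is inflated in the same way.** With over a thousand non-events it hardly moves.
- **That the 10-event figures are the expected case.** Ten is the count of overdoses. The Reference Event section also admits acute events, meaning any staff intervention, and the article gives no count of these. More reference events would mean less optimism.
- **That the sponsor's hold on both signal and labels biases the result.** The article names the device company and does not say that it is the sponsor. Access removes blinding as a safeguard but does not by itself bias a score.
- **That these figures feed the later randomized study.** The article says only that such a study is planned.

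**Conclusion.** The point holds in conditional form. The article assigns the same SIF recordings to training, refining and testing the algorithm, and it scores sensitivity against SIF reference events with no locked version or independent test set. Unless the version is fixed before scoring, the sensitivity will be too high. On the assumptions above, the excess is about 5 to 15 points at the planned 40 events and about 13 to 45 points in an overdose-only analysis of the 10 observed. It would be zero for a version locked beforehand or scored on separate participants. A reader might infer that the published figures are certain to be in-sample; the text does not settle that.

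**What to change.** Amend Algorithm Under Test to commit to one of these routes:

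1. **Locked version.** Score a version fixed before any of this study's labels were used, and identify it. The Results section says analysis is under way, so this is open only if such a version exists.
2. **Participant-level cross-validation.** Keep all visits of a participant in one fold, and nest feature, threshold and version selection inside each fold.
3. **Participant-level bootstrap optimism correction**, repeating the same selection steps in each resample.

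Whichever is chosen, label any figure computed on the development data as *apparent (development) performance*.

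A single hold-out is a poor substitute at these counts. Assuming half the events are held out, 18 of 20 detected gives an exact 95% interval of 0.68 to 0.99, against 0.76 to 0.97 for 36 of 40. With 5 of the 10 overdoses held out, even 5 of 5 gives 0.48 to 1.00. Resampling by participant keeps every event in use.

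The cost is a change of wording, some computing time and a less favourable reported sensitivity. No new data are needed.

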## Results

Funding was granted in July 2023 and dates for data collection are August 2023 to February 2024. As of April 2024, we have enrolled 47 participants, consisting of 17 females and 30 males with an average age of 45 years. Heroin was the preferred drug for most participants (40/47) and then methadone or an opioid agonist treatment (6/47), with the largest proportion injecting 2 to 5 times daily (BD-5D—n=23), and then once daily (14/47). The majority had experienced an overdose in the past (29/47). Among all the participants, a total of 1145 injecting events were recorded while participants wore the sensor, with 10 overdose events being observed. Data analysis of the outcome measures is ongoing.

## Discussion

There has been a recent surge of interest in mobile health and wearable devices to treat opioid use disorders [18,19] and specifically to detect and respond to opioid overdoses. However, there is limited research on detecting true overdose (which requires intervention) and the effectiveness of these devices to detect overdose in the community has not yet been adequately evaluated. A chest sensor that reliably detects the overdose breathing signature could alert the emergency services and save lives when fully developed and used in the community.

This observational study aims to capture chest motion data while participants wear a small chest-worn biosensor within medically supervised injecting centers in Australia. The data collected here will be used to test and develop respiratory “signatures” to accurately detect an acute or potential opioid overdose. Testing will allow for the differentiation of patterns that occur following opioid use but do not result in an overdose.

It is anticipated that this study will capture chest motion data from the sensor while participants inject opioids and it is likely that some instances of potential overdose will also be captured by the sensor. It is uncertain how much chest motion data will be corroborated with staff-measured outcomes. It is anticipated that the sensor will be considered positively overall among participants.

The findings of this study will be compared to a previous study of this chest sensor among participants who wear the sensor at home and are on opioid agonist treatment (paper in preparation), as well as other studies on wearable devices that have been examined acceptability and feasibility of varied technologies to combat the overdose crisis [20-25]. The potential effectiveness and acceptability of these studies are varied. Generally, there is limited but expanding research in this area with studies focused on products or technologies that are relatively new or in early development [12]. There is no published work on a remote chest sensor that can reliably detect chest wall movement in the context of an opioid overdose.

The strengths of this study are that it examines the effectiveness of the chest sensor among people who are injecting opioids in a relatively controlled but real drug-using environment. Research within an SIF is a unique opportunity to address external validity as participants will be those who the sensor is eventually intended for.

However, the study is likely to be limited in a few different ways. First, it is likely that participants will be polydrug users and it may not be possible to examine the effect of opioids alone. Additionally, the number of prompt or acute events is likely to be lower than in other drug-using environments as participants will be users who are using in a safe setting that is aimed at reducing harms and mortality around injecting drug use. This may mean the target number of acute events will be negatively impacted. Other potential limitations could include the physical movement of individuals while using the device interfering with the data capture, or data quality. The more the participants, the better the quality of data will be.

Future development of this work will involve conducting a randomized clinical investigation of a medical device to determine its effectiveness in detecting OIRD. It will also be important to test the device in people’s personal environments, for example, in their homes.

## Appendix

Multimedia Appendix 1 SPIRIT (Standard Protocol Items: Recommendations for Interventional Trials) guidelines.

Multimedia Appendix 2 AVPU (Alert Verbal Pain Unresponsive) scale.

Multimedia Appendix 3 Participant satisfaction survey.

Multimedia Appendix 4 Consent form.

## Abbreviations

ADE: adverse device effect
AVPU: Alert Verbal Pain Unresponsive
AWS: Amazon Web Services
CCPA: California Consumer Privacy Act
CRO: Contract Research Organization
ECG: electrocardiography
GDPR: General Data Protection Regulation
HIPAA: Health Insurance Portability and Accountability Act
HITRUST: Health Information Trust Alliance
MSIC: Medically Supervised Injecting Centre
MSIR: Medically Supervised Injecting Room
OIRD: opioid-induced respiratory depression
SIF: safe injecting facility
SPIRIT: Standard Protocol Items: Recommendations for Interventional Trials
